**Fig 1 pone.0357577.g001:**
[figure not shown]
Study design and comparison groups. Schematic overview of the retrospective multicentric cohort study evaluating the impact of GLP-1 RA therapy on patients with IPMNs. Four study groups will be included according to IPMN diagnosis and GLP-1 RA exposure: patients with IPMN treated with GLP-1 RAs, patients with IPMN not treated with GLP-1 RAs, patients without IPMN treated with GLP-1 RAs, and patients without IPMN and without GLP-1 RA exposure (general population). The primary outcome (1) is the progression of radiological IPMN characteristics according to the Kyoto 2023 Consensus criteria. Secondary outcomes include longitudinal changes in serum CA19−9 and CEA levels (2) and the incidence of acute pancreatitis (3). We hypothesize that GLP-1 RA therapy is not associated with an increased progression of IPMN radiological features or adverse pancreatic outcomes compared with patients not exposed to GLP-1 RAs.

A list of patients diagnosed with IPMNs will be compiled (List A), and this group will then be cross-referenced with data from patients who have been treated with GLP-1 RAs (List B). ICD-10 codes, keywords like IPMN and ATC medication codes will be used to identify the patients and compile the two lists (S1 File). This method will allow us to identify the subset of patients in whom both IPMN and GLP-1 RA treatment are present. The same number of patients will be randomly extracted from the two lists. For example, if 3 patients with GLP1-RA and IPMN are extracted in the HFR dataset, then 3 patients will be extracted in List A and 3 in List B. The same procedure will be carried out for the other two institutions. For the no GLP-1 RA & no IPMN group, the proportion of AP will be generalized to the incidence in the general population.

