### Sample size and statistical analysis

#### Sampling plan.

The sample size is expected to be between 10 and 20 patients for the condition with GLP-1 RAs and IPMN, due to the rare nature of the patient population with both IPMN and GLP-1 RA use. The other conditions (GLP-1 RA & no-IPMN, no GLP-1 RA & IPMN) will match in sample size the above-mentioned condition as it is the most stringent. This design ensures to isolate the interaction effect of GLP-1 RA and IPMN while ensuring proper statistical power. Indeed, a-priori power analysis computed with G*Power [22] shows that for our smallest estimation of effect size (i.e., 10–30 patients per condition, 30–60 in total), a 2x2 ANOVA detects a significant medium effect size with a power if 80% and an alpha of 0.05.

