#### Positive controls.

Groups need to balanced in age, BMI, and in their number of follow-ups. If age between groups is unbalanced, as defined by a Cohen’s d > 0.4, outliers will be removed until this threshold is reached. For the number of follow-ups, follow-ups above the limiting factor will be ignored from the data collection to balance the groups if needed.

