#### Analysis plan.

H1) We expect significantly more occurrences of change in at least one of the criteria from the Kyoto 2023 Consensus (see Outcomes section) [1] from patients with GLP-1 RA & IPMN than patients with no GLP-1 RA & IPMN, as assessed by a one-sided test of two proportions. H2) We expect significantly greater changes in the CEA (H2a) and CA19−9 (H2b) serum tumor markers over time induced by GLP-1 RA, as assessed by the interaction term of the within-factor Time and the between-factor Group (GLP-1 RA & IPMN vs. no GLP-1 RA & IPMN). H3) We expect significantly different incidence of AP driven by GLP-1 RA and IPMN, as assessed by a Chi-square test across all conditions (GLP-1 RA & IPMN, no GLP-1 RA & IPMN, GLP-1 RA & no IPMN).

Timing of progression: T0 will be defined as the first available follow-up examination for patients with IPMN who were not treated with GLP-1 RAs, and as the first available follow-up examination after initiation of GLP-1 RA therapy for patients with IPMN who received GLP-1 RAs.

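### H1 is tested without a hospital stratum although controls are drawn hospital by hospital: valid while balance holds, but conservative and less efficient if hospitals differ

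*Protocol article*

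**What the plan says.** **The draw (Protocol article, Study design, text after the Fig 1 legend).** Control numbers are fixed separately in each hospital. For three dual-condition patients at the first hospital, "then 3 patients will be extracted in List A and 3 in List B". For the rest, "The same procedure will be carried out for the other two institutions". Numbers are matched within hospital; individual patients are not paired.

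**The test (Analysis plan).** H1 compares IPMN patients with and without GLP-1 RA exposure. It expects more Kyoto changes in the exposed "than patients with no GLP-1 RA & IPMN, as assessed by a one-sided test of two proportions". Hospital is not mentioned.

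**The size (Sampling plan).** "The sample size is expected to be between 10 and 20 patients for the condition with GLP-1 RAs and IPMN", and the other groups "will match in sample size the above-mentioned condition as it is the most stringent". H1 therefore compares 10 with 10 up to 20 with 20.

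**After the draw (Positive controls).** If age is unbalanced by Cohen's d above 0.4, "outliers will be removed until this threshold is reached". The text does not say whether hospital is considered when patients are removed.

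**The concern.** Equal numbers within each hospital take hospital differences out of the exposed-versus-control contrast. The ordinary two-proportion test does not use this. Its standard error is built from one overall proportion, so it counts between-hospital variation that the draw has already balanced out. If scanner, surveillance interval or case mix makes the change rate differ between hospitals, the standard error is too large, the test rejects too rarely, and power is lost in a comparison with only 10–20 patients per group.

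A second, weaker strand concerns removals. If age-based removals fall unevenly across hospitals, the balance no longer holds and a crude comparison has nothing that corrects for it.

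**Working it through.** **1. The plan's own power figure.** The Sampling plan claims that "a 2x2 ANOVA detects a significant medium effect size with a power if 80% and an alpha of 0.05". This is not a figure for H1. With Cohen's f = 0.25 (the conventional medium effect; the article gives no number), a between-subject 2×2 ANOVA has 26% power at N = 30 and 48% at N = 60, and needs N = 128 for 80%. The 80% is therefore not reproduced in that form and is not used below. For H1 itself, 20% versus 50% at one-sided 0.05 gives about 40% power at 10 per group and 64% at 20 per group.

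**2. Inputs.** From the article: three hospitals, 1:1 numbers within each, 10–20 per group, a one-sided test. Alpha 0.05 is stated only for the ANOVA and is carried over to H1. Assumed: hospital splits of 4/8/8 (20 per group) and 3/3/4 (10 per group), the control rates shown below, and a common odds ratio of 4 (at 20% the odds are 0.25; 0.25 × 4 = 1, so 50% in the exposed).

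**3. Statistics.**
- Crude: z = (p₁ − p₀) / √[p̄(1 − p̄) · 2/n].
- Stratified (Cochran-Mantel-Haenszel, CMH, no continuity correction): z = Σ(a_h − E_h) / √ΣV_h, with E_h = n₁ₕt_h/N_h and V_h = n₁ₕn₀ₕt_h(N_h − t_h) / [N_h²(N_h − 1)]. Here a_h is the number of exposed patients with a change in hospital h, and t_h is the number of all patients with a change.

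**4. Why the crude test is conservative.** With no drug effect and 1:1 numbers in each hospital, the true variance is proportional to the weighted mean of p_h(1 − p_h), whereas the crude test uses p̄(1 − p̄). With r their ratio, the effective critical value is 1.645/√r. For 4/8/8:

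| Rates | p̄ | p̄(1 − p̄) | Within-hospital mean | r | 1.645/√r | One-sided error |
|---|---|---|---|---|---|---|
| 20/30/40% | 6.4/20 = 0.32 | 0.2176 | 4.24/20 = 0.212 | 0.974 | 1.667 | 4.8% |
| 10/20/40% | 5.2/20 = 0.26 | 0.1924 | 3.56/20 = 0.178 | 0.925 | 1.710 | 4.4% |
| 10/30/60% | 7.6/20 = 0.38 | 0.2356 | 3.96/20 = 0.198 | 0.840 | 1.794 | 3.6% |

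Simulation of the last row gives 3.4–3.5% for the crude test and 5.1% for CMH.

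**5. Power by simulation (200,000 or more runs per scenario), crude versus CMH.**

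| Control rates | 20 per group (4/8/8) | 10 per group (3/3/4) |
|---|---|---|
| 20/20/20% | 64.7% vs 63.9% | 42.4% vs 42.9% |
| 20/30/40% | 64% vs 66% | 45.4% vs 46.1% |
| 10/20/40% | 58.7% vs 63.5% | 37.7% vs 40.3% |
| 10/30/60% | 51.5% vs 61.9% | 33.3% vs 37.3% |

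The gain runs from −0.8 to +0.5 points with equal rates, then 0.7 to 2, 2.6 to 4.8, and 4.0 to 10.4 points.

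**6. If removals break the balance.** Start from 4/8/8 with no drug effect. Remove two exposed patients from the lowest-rate hospital and two controls from the highest-rate one, a pattern chosen to be unfavourable. At 10/30/60% the expected crude proportions are (0.2 + 2.4 + 4.8)/18 = 41.1% in the exposed and (0.4 + 2.4 + 3.6)/18 = 35.6% in controls, a spurious difference of 5.6 points. Crude one-sided error is then 9.6% (6.9% at 10/20/40%), against 5.1% for CMH. If only the two exposed patients are lost, crude error is 4.8–6.2%. Removals in the opposite direction make the crude test more conservative.

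**The case against.** The strongest objection is that no loss has been shown. The article reports no progression rate, overall or by hospital, and with equal rates stratification gains nothing. The 10-point gain needs a six-fold spread between three Swiss tertiary hospitals; a moderate spread is worth about 1–2 points. Some of the design also narrows hospital differences. Two radiologists at one hospital read the imaging (Radiological evaluation), and surplus follow-ups are ignored to balance the groups (Positive controls). All of this stands, and it is why the point is conditional and minor.

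A reader might infer three stronger things that the documents do not support:

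- **That the named test is invalid.** With equal numbers in each hospital, hospital does not confound the crude comparison, and its error is near nominal or below it.
- **That power is certainly lost.** This depends on hospital differences that the article does not quantify.
- **That age-based removal disregards hospital, so a hospital difference will pass for a drug effect.** The text is silent on hospital. Removal is triggered only by an age imbalance, and the error inflates materially only under a particular pattern of losses.

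It can also be said that stratification by site is a detail for an analysis plan that is not shown, and that the Discussion already calls the results hypothesis-generating. The second part is fair and limits the consequence. The first carries less weight: the article does name its primary test, and the test as named does not use the strata that its own sampling creates.

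**Conclusion.** The mismatch between the hospital-wise draw and the unstratified H1 test is real, and it concerns efficiency. With the balance intact, the test is valid and at worst conservative. The gains in the working rest on assumed hospital rates, assumed splits and an odds ratio of 4; only their pattern (nil with equal rates, rising with the spread) is independent of those choices. Protection against uneven removals is a secondary benefit, because the article does not show that such removals would occur. The gain is small beside the main limit, which is 10–20 patients per group.

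**What to change.** In the Analysis plan, replace the H1 test by a one-sided Cochran-Mantel-Haenszel test stratified by hospital. An exact stratified version is reasonable with about 3–8 patients per group per hospital. Report the Mantel-Haenszel risk difference with its interval, and keep the crude two-proportion result as a sensitivity analysis. Fix this before outcome data are analysed.

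The cost is one sentence. Hospital is not in the variable list under Data collection, but it should be recoverable for every patient because the draw is made by hospital; confirm that it is kept in the dataset. The statistical downside is under one point of power if hospitals do not differ.

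### H2 treats irregular routine-care visits as fixed levels of Time and surplus follow-ups may be dropped; with 10–20 patients per group, a mixed model in actual time on all visits would use the marker data better

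*Protocol article*

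**What the plan says.** - **Test.** Analysis plan, H2: the change in CEA and CA19-9 over time is assessed by the "interaction term of the within-factor Time and the between-factor Group", with Group defined as "GLP-1 RA & IPMN vs. no GLP-1 RA & IPMN". This is the wording of a mixed (repeated-measures) ANOVA. ANOVA is also the only model named in the Sampling plan.
- **Size.** Sampling plan: "The sample size is expected to be between 10 and 20 patients for the condition with GLP-1 RAs and IPMN". The other conditions "will match in sample size the above-mentioned condition as it is the most stringent". H2 uses two of these groups, so 20–40 patients.
- **Visits.** Positive controls: "follow-ups above the limiting factor will be ignored from the data collection to balance the groups if needed".
- **Time origin.** Analysis plan, timing of progression: T0 is the first available follow-up examination in unexposed patients, and the first available one after treatment start in exposed patients. No fixed visit schedule is given, as expected for a retrospective study.
- **Not stated.** The article gives no measurement scale for the markers (raw or log), no distribution or SD, no number or spacing of visits, and no definition of the levels of Time.

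**The concern.** A within-patient factor needs levels that mean the same thing in every patient. With routine-care visits, the second or third examination may fall a few months after T0 in one patient and years after it in another. Equalising the number of visits does not equalise elapsed time. If patients on a GLP-1 RA are seen more often than the others, a drift common to both groups shows up as a Time by Group interaction.

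The second problem is loss of data. ANOVA on a within-factor works on a common set of visits, and the rule under Positive controls produces that set by ignoring the surplus. The ignored visits tend to be the later ones, which tell most about a slope. A comparison of 10–20 patients per group can hardly afford this.

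**Working it through.** **1. The plan's own power figure.** The Sampling plan says that "a 2x2 ANOVA detects a significant medium effect size with a power if 80% and an alpha of 0.05". Read medium as Cohen's f = 0.25.

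- 2×2 between-patient interaction, λ = N f², df 1 and N − 4. N = 30: λ = 30 × 0.0625 = 1.875, power 0.26. N = 60: λ = 3.75, power 0.48. Power of 80% needs N = 128 (λ = 8).
- Repeated measures, 2 groups × 2 times, λ = N m f²/(1 − ρ), df 1 and N − 2, with m = 2 and ρ = 0.5 (assumed). N = 34: λ = 34 × 2 × 0.0625/0.5 = 8.5, power 0.81. N = 40: 0.87. N = 30: 0.75. N = 20, the low end for H2: 0.56.

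The 80% is therefore not reproduced for the 2×2 ANOVA named. It appears within 30–60 patients only under unstated repeated-measures settings. That is a separate issue, but it gives no assurance that H2 has information to spare.

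**2. Assumptions for comparing methods.** The article gives none of these values.

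- Log marker SD 0.8 between patients and 0.3 within; slope SD 0.15 per year.
- Gaps between visits uniform on 0.4–1.6 years (mean 1 year).
- Each patient has 0–3 visits beyond the common number (mean 1.5). The visit rule is read strictly: ANOVA uses the common number only.
- True extra slope in the exposed 0.3 log units per year, a ratio of e^0.3 = 1.35 per year.
- Two-sided 5%; 400–600 simulated trials per setting (Monte Carlo error about 2–2.5 points).
- Mixed model: REML, random intercept and slope, actual time, t test on n − 2 df.

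**3. Hand check of one cell.** With two visits the interaction is a t test on change. On the log scale the variance of change is 2 × 0.3² + 0.15² × E(t²). Here E(t²) = 1² + 1.2²/12 = 1.12, so the variance is 0.18 + 0.025 = 0.205 and the SD 0.453. The standardised difference is 0.3/0.453 = 0.66, which gives power 0.29 at n = 10 and 0.53 at n = 20. The simulation gave 0.25 and 0.51, which agrees within its error.

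**4. Power under gradual divergence.**

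| Common visits | n per group | Raw ANOVA | Log ANOVA | Log mixed model, same visits | Log mixed model, all visits |
|---|---|---|---|---|---|
| 2 | 10 | 0.16 | 0.25 | not fitted | 0.81 |
| 2 | 20 | 0.35 | 0.51 | not fitted | 0.98 |
| 3 | 10 | 0.35 | 0.62 | 0.69 | 0.92 |
| 3 | 20 | 0.71 | 0.92 | 0.95 | 1.00 |

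Type I error of the mixed model on all visits was 0.03–0.065.

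**5. Where the gain comes from.**

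- *Retained visits.* Three common visits, n = 10: 0.69 to 0.92, or 23 points. With two common visits the whole step from log ANOVA is 0.81 − 0.25 = 56 points. It was not split there, but the three-visit rows show that retention is the larger part.
- *Actual time on the same visits.* Across the gradual-divergence settings, about 0–8 points over log ANOVA.
- *Log scale.* From almost nothing to 39 points, depending on skew. Log SD 0.4 (within-patient 0.2, slope SD 0.1), two visits, n = 10: 0.50 to 0.54. Log SD 1.0, three visits, n = 10: 0.24 to 0.62.

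**6. Unequal spacing, no true effect.** With a common drift of 0.15 log units a year and exposed patients seen twice as often, log ANOVA on visit number rejected in 6–12% of trials and raw ANOVA in 4–9%. The mixed model rejected in 4–6%.

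**7. Where the mixed model loses.** If the exposed shift by 0.3 log units after T0 and then stay level, power with two common visits was:

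| n per group | Raw ANOVA | Log ANOVA | Mixed model, linear time, all visits |
|---|---|---|---|
| 10 | 0.19 | 0.29 | 0.17 |
| 20 | 0.36 | 0.52 | 0.28 |

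A shift completed before T0 was found by no method (3–8% rejections).

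**8. The random slope is needed.** With a random intercept only, and slope SD 0.15 per year, the mixed model rejected a true null in 16–22% of trials. With a random slope it rejected in 4–7%.

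**The case against.** The strongest reply is that the plan's test is roughly valid when spacing is alike in both groups, while a carelessly specified mixed model is not. This is right: a random-intercept-only model would trade a test near its nominal level for one that rejects a true null about one time in five. The remedy must include the random slope.

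It can also be said that transformation is commonly left to an analysis plan that is not shown. That too is right. A reader might infer that H2 analyses untransformed concentrations and that one or two patients with high markers would decide it. The documents do not support this: no scale, distribution or SD is stated, and a Time by Group interaction can be run on logs. The Introduction's case report of a markedly raised CA19-9 on a GLP-1 RA makes extreme values foreseeable, but it says nothing about the scale. The log scale is advice here, not the correction of an error.

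A reader might also infer that a mixed model is clearly stronger on the same data whatever the truth. It is not. On identical visits it adds little, and with linear time it loses under an early plateau. Nor does a simple before-and-after comparison of log and raw values settle the matter, because T0 in the exposed is already on treatment and H2 makes no such contrast.

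Finally, H2 is secondary and the Discussion calls the results hypothesis-generating. That limits the weight of the point but does not remove it: H2 is still a significance test, and discarding measurements makes its estimate less useful for planning later studies.

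**Conclusion.** The concern holds in a limited form. The article fixes Time as a factor for irregular visits and allows follow-ups to be dropped to equalise counts. Both are stated choices, not details left open. With 10–20 patients per group they waste information, and they can confound group with elapsed time if spacing differs between the groups.

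The size is conditional. It rests on the assumed SDs, on gradual divergence, on a strict reading of the visit rule, and on patients having up to three surplus visits. The rule applies only if needed, so the loss is smaller where visit counts are already similar. This is an improvement the sponsor should make to a secondary analysis; it does not make H2 invalid.

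**What to change.** For H2:

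- Analyse log(CA19-9) and log(CEA) in a linear mixed model with group, actual time since T0 and group × time, a random patient intercept and a random slope, and small-sample degrees of freedom.
- Exempt H2 from the visit-dropping rule under Positive controls and keep all follow-ups.
- Add a flexible or early-change time term as a sensitivity analysis, to cover a plateau.
- Report the ratio of fold-change per year between groups with its 95% confidence interval.

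**Cost.** No new patients. It is more than a change of wording, because the rule takes surplus visits out of data collection and they would now have to be extracted. The model is more complex, and a random slope may be hard to estimate at 10 per group. Results are read as ratios.

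**Limit.** None of this repairs a T0 set after treatment start; a marker change completed before T0 stays invisible to any of these analyses.

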### Population

Inclusion criteria are adult patients (≥18 years old) with a radiological diagnosis of IPMN and/or documented treatment with GLP-1 RAs, availability of medical records including laboratory results and imaging studies and signed informed consent permitting the use of anonymized clinical data for research. Eligible individuals will then be classified into one of four groups:

Patients with GLP-1 RA exposure and IPMNPatients with GLP-1 RA exposure without IPMNPatients without GLP-1 RA exposure with IPMNPatients without GLP-1 RA exposure and without IPMN = general population

Exclusion criteria is refusal of consent for research participation.

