## Discussion

This study aims to provide preliminary insights into the potential impact of GLP-1 RAs therapy on the progression and clinical outcomes of IPMNs. A better understanding of the relationship between GLP-1 RA exposure and IPMNs may help address current safety uncertainties and support clinical decision-making in this complex patient population.

Several limitations must be acknowledged. The retrospective design introduces inherent risks of selection and information bias, while the relatively small sample size limits statistical power and the ability to detect modest associations. Patient identification may be incomplete, as GLP-1 RAs prescriptions may have been initiated by healthcare providers outside the participating institutions or inconsistently documented and therefore not fully captured in institutional records. Furthermore, initiation of the treatment may have been influenced by clinical judgement and recent literature implying a possible link between GLP1 Ras use and pancreatitis or pancreatic cancer, introducing potential prescription bias. In addition, the relatively recent and rapidly increasing widespread use of GLP-1 receptor agonists may limit the ability to assess long-term effects on IPMN evolution. As a result, potential late modifications or clinically relevant changes may not yet be detectable within the available follow-up period.

Therefore, the results should be interpreted as hypothesis-generating. Despite these limitations, this study addresses an important gap in the current literature and may serve as a basis for future prospective, multicentre studies.

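### H3 compares raw acute pancreatitis incidence without using earlier pancreatitis, although the protocol says a suspected pancreatitis link may have influenced who was prescribed GLP-1 RAs

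*Protocol article*

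**What the plan says.** The Analysis plan section of the protocol article fixes the test for H3: "We expect significantly different incidence of AP driven by GLP-1 RA and IPMN, as assessed by a Chi-square test across all conditions". The conditions it lists are "GLP-1 RA & IPMN, no GLP-1 RA & IPMN, GLP-1 RA & no IPMN". The fourth cell of the 2 × 2 design is not sampled; the text under Fig 1 takes its AP proportion from the general population.

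The other passages that could bring earlier pancreatitis into H3 do not do so:

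- **Eligibility (Population):** "Exclusion criteria is refusal of consent for research participation". This is the only exclusion.
- **Sampling (text under Fig 1):** "The same number of patients will be randomly extracted from the two lists". The draw is matched on number within each hospital and on nothing else.
- **Balance (Positive controls):** "Groups need to balanced in age, BMI, and in their number of follow-ups".
- **Endpoint (Secondary outcomes and H3):** simply "incidence of AP", with no distinction between first and recurrent episodes.
- **Timing (Analysis plan):** T0 is defined under the label of progression timing, and only for the two IPMN groups.
- **Data (Data collection):** clinical history is extracted, but pancreatitis is not among the items named.

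Among its limitations, the Discussion says that "initiation of the treatment may have been influenced by clinical judgement and recent literature implying a possible link between GLP1 Ras use and pancreatitis". The same sentence also mentions cancer of the pancreas, and it describes the consequence as "introducing potential prescription bias". No analysis in the article responds to that statement.

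**The concern.** When a feared outcome influences who receives a drug, the reason for not prescribing can itself predict that outcome. Here the feared outcome includes pancreatitis, and H3 compares pancreatitis. Patients with an earlier episode are an obvious group in whom such caution might operate. If it did, they would be under-represented in both GLP-1 RA groups and would remain in the unexposed IPMN group, which is a random draw from List A. An unadjusted comparison would then mix any drug effect with a difference in the tendency to recur.

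This is separate from the question of when follow-up begins. Even if only new episodes after a well-defined start were counted, the recurrence-prone patients would still sit mainly on the unexposed side.

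Fig 1 hypothesises no increase in adverse pancreatic outcomes with GLP-1 RAs, and the Discussion hopes the study will support clinical decisions. A distortion toward that reassuring answer is therefore the one most worth guarding against.

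**Working it through.** **The plan's own figures.** The article gives no power, expected rate or effect size for H3. Its only power statement concerns a 2 × 2 ANOVA, and this point does not depend on it.

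**Inputs from the article.** There are 10 to 20 patients in the co-exposed group, and the other sampled groups are matched to it (Sampling plan). H3 is an unadjusted chi-square over three groups.

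**Inputs assumed, because the documents give none:**

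- AP risk in follow-up without earlier AP: r0 = 3%.
- AP risk in follow-up with earlier AP: r1 = 15% or 25%.
- Share with earlier AP among unexposed patients: qU = 10%, 20% or 30%.
- Share with earlier AP among exposed patients: qE = 0% or 5%.
- The drug multiplies risk by the same factor, RR, whether or not there was earlier AP.

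**Formula.** Apparent risk ratio = RR × [qE·r1 + (1 − qE)·r0] / [qU·r1 + (1 − qU)·r0].

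**No drug effect (RR = 1), ends of the range:**

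- Weakest distortion (qU 10%, qE 5%, r1 15%): (0.05×0.15 + 0.95×0.03) / (0.10×0.15 + 0.90×0.03) = 0.036 / 0.042 = 0.86.
- Strongest distortion (qU 30%, qE 0%, r1 25%): 0.03 / (0.30×0.25 + 0.70×0.03) = 0.03 / 0.096 = 0.31.

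**True doubling (RR = 2).** The same two cases give 2 × 0.857 = 1.71 and 2 × 0.3125 = 0.63.

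**Sensitivity to the assumed rates.** A second set uses r0/r1 of 2%/20% or 5%/30%, with (qE, qU) of (0%, 10%), (0%, 20%), (5%, 20%) or (5%, 30%). The apparent ratio is 0.36 to 0.67 with no effect and 0.71 to 1.33 with a true doubling.

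**Restriction.** Setting qE = qU = 0 gives RR × r0 / r0 = RR, so in these scenarios restriction to patients without earlier AP returns 1.0 or 2.0.

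**What this means in patients.** In the strongest case, expected events per group are:

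| Group size | Unexposed (9.6%) | Exposed (3%) |
|---|---|---|
| 10 | 0.96 | 0.30 |
| 20 | 1.92 | 0.60 |

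One event moves a group's incidence by 1/20 = 5 to 1/10 = 10 percentage points. Enumerating the three-group chi-square at 0.05, with both exposed groups at the exposed risk, gives a significant result in about 4% (n = 10) or 11% (n = 20) of studies in the strongest case. In the weakest case it is about 1% to 3%.

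**The case against.** The strongest reply has five parts.

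- **The key link is inferred.** A reader might take the Discussion to say that GLP-1 RAs were withheld from patients with earlier AP. It does not. It says initiation may have been influenced by clinical judgement and by literature on pancreatitis or pancreatic cancer. Clinicians may have been reacting to the IPMN and the cancer question, in which case earlier AP need not differ by exposure. This stands; the steering is plausible, not documented.
- **The net direction is unknown.** A reader might infer that the drugs will look safe or protective. The documents do not support that either. Exposed IPMN patients were treated for diabetes or obesity, whereas the List A draw is not selected on these; BMI is to be balanced, but diabetes and lipids are not. Such confounding could act in the opposite direction. This stands.
- **The size rests on assumption.** None of the four rates is in the documents, and the imbalance in earlier AP is an input to the illustration, not a result. This stands.
- **Chance will dominate.** With around one event per group, the distortion would rarely yield a significant chi-square, and H3 is a non-directional three-group test, not a risk ratio. AP is also one of two secondary outcomes, so calling it the main safety outcome would overstate its place. All true. But the observed incidences will still be read, and one or two recurrent cases can set their order.
- **It is disclosed, and other documents may handle it.** Prescription bias and the hypothesis-generating status are stated, and an SAP or the REDCap form may hold more. Disclosure does not change the comparison, though, and the article itself fixes the test, the exclusion and the balancing factors.

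**Conclusion.** The point holds in a limited form. As written, H3 leaves a plausible confounder, earlier AP, in a safety comparison, and the protocol itself gives a reason to expect it. If patients with earlier AP were less often prescribed GLP-1 RAs, this component would push H3 toward no harm. Under the assumed rates, a drug with no effect would show a risk ratio of about 0.3 to 0.9, and a true doubling would show about 0.6 to 1.7.

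Those ranges show what could happen; they are not estimates for this study. They rest on assumed recurrence risks, an assumed imbalance and a constant relative effect. The documents establish neither the imbalance nor the net sign of all confounding. It would also go too far to say that data already collected can remove the problem, because pancreatitis is not a named history item and only documented episodes can be acted on. The change is worth making because it is inexpensive, not because a reversal of the result has been shown.

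**What to change.** 1. Add documented AP before the start of risk as an explicit item for every sampled patient.
2. Define that start of risk for all three sampled groups, including GLP-1 RA & no IPMN, which has none at present. Use the same look-back in each. The existing T0 definitions would not do: the first follow-up after drug initiation in exposed patients and the first available follow-up in unexposed patients would often give the exposed a longer screening period.
3. Count only AP that occurs after the start of risk.
4. Tabulate earlier AP by group.
5. Report H3 in patients without earlier AP, with replacement draws from Lists A and B where needed and an exact test given 10 to 20 patients per group. Place it beside the all-patient comparison, and show patients with earlier AP separately by exposure. Co-exposed patients with earlier AP stay in H1 and H2.

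The cost is one more extracted item, a start-of-risk rule that has to be written for three groups, and a short addition to the H3 analysis. A few co-exposed patients, the scarcest group, leave the restricted comparison and cannot be replaced, so group sizes may become unequal. The restricted result applies only to patients without earlier AP and removes only confounding by documented earlier AP. Undocumented episodes, diabetes, obesity and other reasons for prescribing remain.
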